### **Objectives**

The primary objective of this trial is to test whether a personalized vitamin D_3_ dosing regimen reduces or prevents fatigue (primary outcome) among stage I-III CRC patients with season-adapted vitamin D insufficiency or deficiency.

The secondary objectives are to assess the efficacy of the treatment on sub-domains of fatigue (physical, emotional and cognitive), QoL (overall and domain-specific), probable depression, functional well-being (FWB), infection frequencies, and various biomarkers (25(OH)D, HbA_1c_, white blood cell count, leukocyte subtype counts, serum c-reactive protein (CRP), uric acid, creatinine, triglycerides, total, low-density lipoprotein (LDL) and high-density lipoprotein (HDL) cholesterol). The study further aims to evaluate the safety of the treatment regarding the occurrence of hypervitaminosis D, hypercalcemia, hypercalciuria, and renal dysfunction.

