**Fig. 1 Fig1:**
[figure not shown]
Overview of the study flow. Abbreviations: *EORTC QLQ-FA12* European Organization for Research and Treatment of Cancer – Cancer related Fatigue; *EORTC QLQ-C30* European Organization for Research and Treatment of Cancer – Core Quality of life questionnaire with 30 items; *FACIT-F* Functional Assessment of Chronic Illness Therapy-Fatigue; *FACIT-F FWB* Functional Assessment of Chronic Illness Therapy-Fatigue – Functional Well-being; *GDS-15* Geriatric Depression Scale with 15 items; *UICC* Union for International Cancer Control

In total, 456 eligible CRC patients are being randomized in order to analyze 410 for the primary endpoint after an expected drop-out rate of 10%. The trial schedule is presented in Table 3.

**Table 3 Tab3:** Detailed schedule of all observations to be performed during the clinical trial

Procedure	Screening Visit for eligibility	Visit 1 Start of treatment	Visit 2 End of rehabilitation	Collection of data via questionnaire/ phone and blood/urine sampling by GP
Rehabilitation clinic	Admission	–	Discharge	–
Time-point of data assessment	–	Day 1	Day 12–21	Week 13–16
Planned doses of vitamin D_3_ per day	–	Individualized initial dose (20,000 or 40,000 IU, followed by 2000 IU per day) for day 1–11	Maintenance dose of 2000 IU per day for day 12–21	–
Inclusion/exclusion criteria	●	●		
Written informed consent	●			
Randomization		●		
Trial medication intake		●	●	
Subject diary regarding days of drug administration		●	●	
Physical examination (weight, height, waist circumference)	●			
Urinary pregnancy test for women of childbearing potential	●			
Assessment of CRC treatment	●			●
Concomitant diseases / Medical history	●			
Concomitant medication	●			●
Query about concomitant use of vitamin D_3_ or vitamin D analogs in self-medication in addition to trial medication				●
Fatigue	●			●
Functional well-being, QoL, infection frequency, and depression	●			●
Blood sampling for biomarker efficacy and safety endpoints	●		●	●
Urine sampling for safety endpoints	●		●	●
(S)AE recording and protocol deviations		●	●	●

Abbreviations: *CRC* colorectal cancer; *GP* general practitioner; *QoL* Quality of life; *SAE* Serious adverse event

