A priori defined subgroup analyses will be conducted for groups defined by age (< 65 / ≥ 65 years), sex (male / female), CRC stage (I or II / III), 25(OH)D levels at screening (< 30 / ≥ 30 nmol/L), season at screening (Dec-Feb/Mar-Mai/Jun-Aug/Sept-Nov), BMI at screening (< 30 / ≥ 30 kg/m^2^), FACIT-F fatigue subscale at screening (≤ 34 / > 34 points), mild to moderate anemia at screening (hemoglobin 8–10 mg/dl / > 10 mg/dl), chemotherapy and/or radiotherapy in 9 months before screening (yes / no), chemotherapy and/or radiotherapy during trial (yes / no), geriatric depression scale (GDS-15) score at follow-up (< 5 / ≥ 5 points), insomnia at follow-up (EORTC QLQ-C30 insomnia item < 3 / ≥ 3 points), pain at follow-up (EORTC QLQ-C30 pain scale < 6 / ≥ 6 points), use of strong opioids (ATC codes N02AB03, N02AA01, N02AG01, N02AA51, N02AA03, N02AG04, N02AA53, N02AA05, N02AJ18, N02AJ19, N02AA55, N02AA56, N02AJ17, N02AX06, N02AE01, and N02AA25) at follow-up (yes / no), use of psycholeptics (ATC code N05) at follow-up (yes / no), and use of corticosteroids for systemic use (ATC code H02) at follow-up (yes / no).

In addition, a subgroup analysis will be conducted for study participants, who most likely profit from the vitamin D_3_ intervention because the following conditions apply combined (yes / no): No protocol deviations (patients did not withdraw consent during the trial, were adherent to the trial medication (defined as taking at least 80% of all capsules), and did not take vitamin D_3_ or vitamin D analogs in addition to the trial medication), FACIT-F fatigue subscale ≤34 at screening, and neither use of strong opioids nor psycholeptics at follow-up.

A mean difference ≥ 3 FACIT-F fatigue subscale points will be considered a clinically relevant difference [19].

Depending on the availability of future funding for genotyping of all randomized trial participants, further subgroup analyses are planned that stratify trial participants by genetic susceptibility for low 25(OH)D levels or cancer related fatigue [38, 39].

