As a sensitivity analysis, a linear regression model will be carried out with FACIT-F fatigue subscale as the dependent variable and treatment group as the independent variable. The linear regression model will be adjusted for all variables named in the subgroup analysis while using some variables continuously instead of categorically (age, hemoglobin levels at screening, 25(OH)D levels at screening, BMI at screening, FACIT-F fatigue subscale at screening, insomnia scale at follow-up and pain scale at follow-up). If appropriate, missing covariate values will be imputed with multiple imputation.

All secondary endpoints with a continuous scale will be analyzed with the same statistical methods as described for the primary endpoint. All dichotomous secondary endpoints will be tested with a Chi^2^ test. AEs will be analyzed with descriptive statistics including frequencies of SAEs.

Lastly, the success of the personalized vitamin D_3_ intervention in raising the serum 25(OH)D level will be evaluated in the intervention group at trial day 12–21. Furthermore, the success of the maintenance dose to maintain sufficient vitamin D status in the intervention group will be evaluated in trial week 13–16. To be successful, the mean 25(OH)D levels in the group with personalized vitamin D_3_ intervention should be higher than 50 nmol/L. This translates into the following test hypotheses:
H_0_: Mean 25(OH)D_personalized intervention_ ≤ 50 nmol/LH_1_: Mean 25(OH)D_personalized intervention_ > 50 nmol/L

To test these hypotheses, we will conduct a one-sample t-test on the mean 25(OH)D levels at a one-sided significance level of 0.025. 25(OH)D levels may be log-transformed if this improves the approximation of a normal distribution (to be tested with a Shapiro-Wilks test).

*Exploratory sub-project: “Determinants of the achieved 25(OH)D levels by the personalized vitamin D*_*3*_*intervention”*

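### The sensitivity regression, 7 of the 16 subgroup factors and the 'most likely profit' subgroup condition on post-randomisation variables, so they are open to bias as estimates of the treatment effect

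*Protocol article*

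**What the plan says.** All of this is in the protocol article, mainly under Statistical methods.

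- **Subgroups.** Sixteen a priori factors are listed. Nine are fixed at or before screening: age, sex, stage, prior chemo/radiotherapy, and screening 25(OH)D, season, BMI, FACIT-F and anaemia. Seven are not: chemo/radiotherapy during the trial, and six follow-up variables. These begin with "geriatric depression scale (GDS-15) score at follow-up (< 5 / ≥ 5 points), insomnia at follow-up" and continue with pain, strong opioids, psycholeptics and systemic corticosteroids.
- **Enriched subgroup.** Patients thought most likely to profit must have no protocol deviation (no consent withdrawal, at least 80% of capsules taken, no added vitamin D). They must also meet this condition: "FACIT-F fatigue subscale ≤34 at screening, and neither use of strong opioids nor psycholeptics at follow-up".
- **Sensitivity regression.** "The linear regression model will be adjusted for all variables named in the subgroup analysis while using some variables continuously instead of categorically". The variables to be used continuously include "FACIT-F fatigue subscale at screening, insomnia scale at follow-up and pain scale at follow-up". GDS-15 is not among them, so it enters as below 5 versus 5 or more.
- **Status of depression.** The Objectives list as efficacy targets "QoL (overall and domain-specific), probable depression, functional well-being (FWB"). Outcomes and endpoints makes the between-group difference in GDS-15 at week 13–16 an endpoint, and the abstract's Discussion expects a treatment effect on depression.
- **Availability at screening.** Table 3 schedules the row "Functional well-being, QoL, infection frequency, and depression" at screening as well as at week 13–16, and does the same for concomitant medication.

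**The concern.** Randomisation makes the arms comparable on everything fixed before treatment starts. It gives no such protection once patients are adjusted for, or sorted by, something that treatment may have altered. GDS-15, insomnia and pain are recorded in the same week 13–16 assessment as the FACIT-F. They may lie on the path from treatment to fatigue, follow from fatigue, or share causes with it. In each case, if treatment moves them, holding them constant no longer estimates the total effect that the primary analysis targets. The text gives no mediation rationale that would make a different target intended.

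The stake is interpretation. The only covariate-adjusted check on a confirmatory result could make a real effect look fragile, or a null effect look harmful. The enriched subgroup could be read as evidence in responders although its two arms were selected partly on behaviour and drug use after randomisation.

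**Working it through.** **1. The plan's own figures.** Sample size estimation gives a difference of 3 points, SD 10.8, two-sided 0.05 and 80% power.

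- Normal approximation: n = 2 × (1.960 + 0.842)² × (10.8/3)² ≈ 203.5, so 204 per group.
- The t-test calculation gives 204.4, so 205 per group and 410 in all.
- 410/0.9 = 455.6, so 456 randomised.

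The stated figures reproduce. Nothing in this point changes them.

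**2. Count.** 9 factors at or before screening + 7 after randomisation = 16.

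**3. Is a conditioning variable one that treatment is expected to change?**

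| Variable | What the article says |
|---|---|
| GDS-15 at follow-up | Declared endpoint; treatment effect expected |
| Insomnia, pain at follow-up | Not among the QLQ-C30 scales chosen as endpoints; a treatment effect is plausible but not stated |
| Opioids, psycholeptics, corticosteroids at follow-up; chemo/radiotherapy during trial | No statement that treatment changes them |

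**4. Size, as an illustration.** Consider a linear model with one follow-up symptom, scaled to SD 1, and no interaction:

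adjusted estimate = total effect − r × g × 10.8

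Here g is the improvement in the symptom caused by treatment, in SD units, and r is the strength of the within-arm correlation between symptom and fatigue. Neither is in the documents. I assume a total effect of 3, r of 0.4 to 0.6 and g of 0.1 to 0.3.

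| g | r = 0.4 | r = 0.6 |
|---|---|---|
| 0 | 3.00 | 3.00 |
| 0.1 | 3 − 0.432 = 2.57 | 3 − 0.648 = 2.35 |
| 0.3 | 3 − 1.296 = 1.70 | 3 − 1.944 = 1.06 |

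**5. Large-sample simulation** (1,000,000 records per scenario, true effect 3 points). The mediator columns use r = 0.6. In the shared-cause column the symptom does not act on fatigue, and the implied correlation is 0.6 × 0.6 = 0.36. The dichotomised covariate splits off the worst 30%.

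| g | Continuous, mediator | Dichotomised, mediator | Continuous, shared cause only |
|---|---|---|---|
| 0 | 3.0 | 3.0 | 3.0 |
| 0.1 | 2.3 | 2.6 | 2.6 |
| 0.2 | 1.7 | 2.3 | 2.2 |
| 0.28 | 1.2 | 1.9 | 1.9 |
| 0.4 | 0.4 | 1.5 | 1.4 |

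Subgroups behave in the same way. At g = 0.28 in the mediator case, the within-subgroup differences were about 2.05 (symptom absent) and 1.66 (present), both below the true 3. With a true effect of zero and g = 0.28, continuous adjustment gave about −1.8 (mediator) or −1.1 (shared cause).

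**6. Limits.** A shift of 0.3 SD slightly exceeds the effect assumed for fatigue itself (3/10.8 = 0.28 SD), so the upper end is generous. The calculation uses one covariate. The plan enters several together, and their joint effect was not computed.

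**The case against.** The strongest reply is that little hangs on these analyses. The confirmatory result is the unadjusted between-group comparison of the FACIT-F at week 13–16, and neither that test nor the sample size depends on any follow-up covariate. This stands, and it limits the severity. A reader might infer that the primary result is biased; nothing in the documents supports that.

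A reader might also infer that all seven factors do bias the estimates. That is too strong. In the regression, bias for the total effect requires treatment to change the covariate, and the article states that expectation only for depression. GDS-15 also enters dichotomised, where the illustrated loss is smaller.

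Nor does the plan lack any clean use of the screening FACIT-F. The change from baseline is a secondary endpoint compared between arms by the primary methods, with no follow-up covariate. The regression is only the sole covariate-adjusted model named for the FACIT-F.

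The no-withdrawal condition adds nothing special to the enriched subgroup, because the stated intention-to-treat population already excludes patients who withdrew consent.

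What remains is that the article itself fixes these covariates and subgroup definitions, so they are not a detail left to an unseen analysis plan, and at least one of them is a declared outcome.

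**Conclusion.** The point holds in this limited form. The sensitivity regression, seven of 16 subgroup factors and the enriched subgroup condition on post-randomisation variables. Their estimates are open to bias of unknown size as estimates of the total treatment effect. The basis in the documents is firm for GDS-15; for the other six factors the exposure is possible but not shown.

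The illustrated fall from 3 points to between 2.6 and 1.1 rests on the assumed correlation and symptom shift and on a single continuous covariate. It shows that the distortion could matter against the protocol's 3-point relevance threshold, not that it will. The primary test and the change-score endpoint are unaffected. Severity: should be fixed.

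**What to change.** - **Regression and efficacy subgroups.** Replace the follow-up values of GDS-15, QLQ-C30 insomnia and pain, strong opioids, psycholeptics and systemic corticosteroids with their screening values. Drop chemo/radiotherapy during the trial as a factor and keep the listed factor for the nine months before screening.
- **'Most likely profit' subgroup.** Define it by screening criteria only: FACIT-F of 34 or less, and no strong opioids or psycholeptics at screening. Leave adherence and added vitamin D to the per-protocol analysis, which already covers both.
- **Anything still defined by follow-up state.** Label it exploratory, and do not present it as a sensitivity check on the primary result or as efficacy evidence.

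No new data are needed. Table 3 collects depression, quality of life and concomitant medication at screening, and the exploratory 25(OH)D sub-project already uses baseline GDS-15 and baseline QLQ-C30 pain. The cost is an amendment of the protocol wording before analysis and the loss of follow-up-state subgroups as efficacy evidence.

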**Infection frequency** will be assessed by a self-developed questionnaire. Participants will be asked to state the number of infection episodes for the following infections during the last 12 weeks: Infections of the upper and lower respiratory tract, gastrointestinal infection with diarrhea, cystitis, and fever higher than 38 °C. The total infection frequency will be the sum of all reported infection episodes. If this sum is lower than the number of stated fever episodes with ≥38 °C, the latter will be used as the total infection frequency. Endpoints will be the mean differences in infection frequencies (total, upper respiratory, and lower respiratory tract infections) between intervention and placebo group at trial week 13–16.

Finally, serum und urine parameters will be measured at every sample collection to evaluate the following secondary endpoints:
Mean difference in levels of total serum 25(OH)D between intervention and placebo group at trial day 12–21 and in trial week 13–16 as well as mean difference in change of levels of total serum 25(OH)D from baseline to trial day 12–21 and from baseline to trial week 13–16.Mean serum 25(OH)D levels > 50 nmol/L in intervention group at trial day 12–21 and in trial week 13–16.Mean differences in levels of biomarkers (white blood cell count (WBC), leukocyte subtype counts (band neutrophils, segmented neutrophils, eosinophils, basophils, lymphocytes, and monocytes), serum CRP, serum uric acid, serum creatinine, serum total cholesterol, serum LDL cholesterol, serum HDL cholesterol, and serum triglycerides between intervention and placebo group at trial day 12–21 and in trial week 13–16 as well as mean difference in change of levels of these biomarkers from baseline to trial day 12–21 and from baseline to trial week 13–16.Mean difference in HbA_1c_ levels between intervention and placebo group at trial week 13–16 as well as mean difference in change of HbA_1c_ levels from baseline to trial week 13–16.Differences in frequency of safety parameters (including hypervitaminosis D, hypercalcemia, hypercalciuria, and renal dysfunction (estimated glomerular filtration rate (eGFR) < 30 ml/min/1.73 m^2^) between intervention and placebo group at trial day 12–21 and in trial week 13–16.Mean differences in levels of safety parameters (including albumin-corrected serum calcium, urine calcium/creatinine ratio, and eGFR) between intervention and placebo group at trial day 12–21 and in trial week 13–16.

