In the following, we describe the statistical methods of an observational sub-project for the secondary outcome “25(OH)D level”. This solely observational research project shall be addressed in those 228 VICTORIA trial participants who received the personalized vitamin D_3_ intervention and adhered to the trial medication (defined by taking at least 80% of the trial medication capsules), which will result in a final sample size *n* < 228. If 25(OH)D levels or log-transformed 25(OH)D levels are normally distributed (to be tested with a Shapiro-Wilks test), a linear regression model will be carried out with a continuous 25(OH)D level variable. In addition, a logistic regression model will be used with a dichotomized 25(OH)D level variable (< 50 nmol/L / ≥ 50 nmol/L) as the dependent variable.

Covariates for the linear and logistic regression model will be study center, age, sex, baseline 25(OH)D, compliance up to time of blood sampling, difference between exactly calculated and rounded supplied loading dose, number of days between last intake of trial medication and blood sampling, season at recruitment, baseline BMI, baseline waist circumference, baseline smoking, baseline physical activity, baseline physical functioning (EORTC QLQ-C30 subscale), baseline Charlson Comorbidity index, baseline frailty, baseline FACIT-F fatigue subscale, GDS-15 total score ≥ 5 points (at baseline), baseline anxiety (GAD-7 score), baseline pain (EORTC QLQ-C30 pain scale), CRC stage, time since CRC tumor surgery, stoma, concomitant use of vitamin D products (at follow-up), chemotherapy and/or radiotherapy in 9 months before trial (yes / no), chemotherapy and/or radiotherapy during trial (yes / no), concomitant use of laxatives (at baseline and/or follow-up), concomitant use of other drugs limiting vitamin D_3_ bioavailability at baseline and/or follow-up (phenytoin, barbiturates, systemic glucocorticoids, rifampicin, isoniazid, cholestyramine, orlistat, dactinomycin or systemic azole-antimycotics), nutritional vitamin D intake (at follow-up), appetite loss (at baseline and/or follow-up), sun exposure in last summer before baseline, skin type, solarium use in last 2 months before baseline, frequency of diarrhea (at baseline and/or follow-up), vitamin D binding protein levels and single nucleotide polymorphisms (SNPs) previously shown to be associated with low 25(OH)D levels. If appropriate, missing covariate values will be imputed with multiple imputation.

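### The 25(OH)D success test is written for the arithmetic mean but may be run on logs, and a mean above 50 nmol/L does not by itself show that patients remain sufficient at week 13–16

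*Protocol article*

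**What the plan says.** Outcomes and endpoints lists as a secondary endpoint "Mean serum 25(OH)D levels > 50 nmol/L in intervention group at trial day 12–21 and in trial week 13–16". Statistical methods turns this into a decision rule, which opens "To be successful, the mean 25(OH)D levels in the group with personalized" and requires that mean to exceed 50 nmol/L. H0 (mean at most 50) and H1 (mean above 50) are both written for the mean in nmol/L. The test is fixed: "we will conduct a one-sample t-test on the mean 25(OH)D levels at a one-sided significance level of 0.025". The next sentence adds that "25(OH)D levels may be log-transformed if this improves the approximation of a normal distribution", to be judged by a Shapiro-Wilk test. The hypotheses are not restated for the log scale.

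The rule serves two questions. At day 12–21 it asks whether the personalised regimen raised the serum level. For the later time point, "the success of the maintenance dose to maintain sufficient vitamin D status in the intervention group will be evaluated in trial week 13–16".

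Shares of patients below 50 nmol/L appear only in the exploratory sub-project on determinants of the achieved level. That sub-project covers verum patients who "adhered to the trial medication (defined by taking at least 80% of the trial medication capsules", and it breaks the shares down by factors that prove statistically significant.

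**The concern.** There are two separate weaknesses.

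First, a t-test on log values against log(50) is a test about the geometric mean. The written H0 is about the arithmetic mean. Because the scale is chosen after looking at the data, and the wording is permissive, the same stated hypothesis may be tested in one of two forms that are not equivalent. Near the limit, pass or fail can turn on which is used.

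Second, sufficiency belongs to a patient. The protocol takes 50 nmol/L from an insufficiency threshold (Definition of season-adapted vitamin D insufficiency), and the sub-project classifies each patient at 50. A group mean above that value is compatible with many patients below it. This matters most for the week 13–16 conclusion, which is phrased in terms of sufficient status. The Discussion presents the personalised loading dose as novel and the trial as a possible base for policy change, so a success statement may be read as saying that the treated patients became and stayed sufficient.

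**Working it through.** **Inputs from the protocol.** Threshold 50 nmol/L, one-sample t-test and one-sided 0.025 (Statistical methods); 205 analysable patients per group (Sample size estimation); 80 nmol/L as the level the loading equation was developed to reach (Intervention arm).

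**Assumptions.** The protocol gives no SD, CV, distribution or sample size for achieved 25(OH)D. I assume n = 205 verum patients with a sample, SD 15 to 30 nmol/L for normal data, and CV 0.3 to 0.5 for right-skewed (lognormal) data.

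**The plan's own figure.** There is none for this rule. The sample size from which I take n does reproduce. A two-sample t-test with difference 3, SD 10.8, two-sided 0.05 and 80% power needs 204.4, so 205 per group. Then 410 / 0.9 = 455.6, so 456 randomised.

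**Step 1: edge of the rule, normal data.** The smallest passing mean is 50 + t(0.975, 204) × SD/√205 = 50 + 0.1377 × SD. For SD 15, 20, 25 and 30 this is 52.1, 52.8, 53.4 and 54.1. The share below 50 at that point is Φ(−0.1377) = 44.5%, whatever the SD. With n = 228 it is 44.8%.

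**Step 2: edge of the rule, lognormal data.** With s² = ln(1 + CV²), the geometric mean (GM) equals the arithmetic mean (AM) × exp(−s²/2).
- Untransformed test: AM needed = 50 / (1 − 0.1377 × CV).
- Log test: GM needed = 50 × exp(0.1377 × s), so AM needed = GM × exp(s²/2).
- Share below 50 = Φ((ln 50 − ln GM)/s).

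| CV (assumed) | Untransformed: AM needed | Share below 50 | Log: AM needed | Share below 50 |
|---|---|---|---|---|
| 0.3 | 52.2 | 50.1% | 54.4 | 44.5% |
| 0.4 | 52.9 | 51.8% | 56.8 | 44.5% |
| 0.5 | 53.7 | 53.4% | 59.7 | 44.5% |

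**Step 3: how often each version passes.** Lognormal data, n = 205, CV 0.4, 20,000 simulated trials:

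| True AM | Untransformed passes | Log passes |
|---|---|---|
| 50 | 2.0% | 0.0% |
| 54 | 77% | 3% |
| 56 | 98% | 31% |
| 60 | 100% | 98% |

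At a true mean of 50, the untransformed test rejects in 2.2%, 2.0% and 1.7% of trials for CV 0.3, 0.4 and 0.5, against the nominal 2.5%. It does not need a normality check at this sample size.

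**Step 4: away from the edge.** If the mean reached 80, the share below 50 would be Φ(−30/SD) = 2.3%, 6.7%, 11.5% and 15.9% for SD 15, 20, 25 and 30 (normal data).

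**The case against.** - **The edge is not the expected result.** A reader might infer that the plan will call a regimen successful while about half the patients stay insufficient. The documents do not support that as a forecast. Any one-sample mean test that is just significant at n = 205 leaves 44.5% below the threshold under normality. If dosing gets near its 80 nmol/L aim, few patients would be below 50. This stands, and it limits the point to what the rule can show by itself.
- **The log option produces no extra false success.** A reader might also infer that choosing the scale after seeing the data makes success easier. It does not. The arithmetic mean is never below the geometric mean, so passing on logs also supports the stated H1, and the simulated log rejection rate at a mean of 50 is zero. The cost is lost power and an estimand that depends on the data.
- **A mean does answer part of the question.** The endpoint, hypotheses and test all use the mean, and at day 12–21 the question is whether the level was raised. Aiming at 80 while requiring more than 50 is no contradiction. This stands; the difficulty is the week 13–16 wording.
- **Untransformed testing is looser on the share below 50.** For lognormal data the log test concerns the median, and just passing it leaves 44.5% below 50 rather than 50% to 53%. That is true, and it is why the proportion should be reported instead of being inferred from either test.
- **Other outputs help.** Statistical methods promises 95% confidence intervals for all outcomes by group, and the sub-project fits a logistic model at the 50 nmol/L cut-off at both time points. The intervals would show whether the mean is 53 or 80. The sub-project covers adherent patients only, so neither output gives the share for the whole verum arm.

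**Conclusion.** The point holds as a minor one. The stated hypotheses concern the arithmetic mean, while the permitted log test concerns the geometric mean. Under the assumed CV of 0.3 to 0.5 and n = 205, that moves the passing arithmetic mean from about 52–54 to about 54–60 nmol/L. The error is on the conservative side: a mean truly above 50 may be missed.

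A mean above 50 also does not alone establish that sufficient status is kept at week 13–16. At the edge of the rule 44.5% are below 50 under normality, a figure that needs no SD, or 50% to 53% under the assumed lognormal data. If the mean reached 80, this falls to 2% to 16% (normal, assumed SD 15 to 30).

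The figures do not justify dropping the mean criterion. A proportion with no threshold attached would leave no decision rule at all. The primary fatigue analysis and the sample size are untouched, and the protocol says the planned interim 25(OH)D analyses have no bearing on the conduct of the trial.

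**What to change.** 1. Run the one-sample t-test on untransformed 25(OH)D at both time points and delete the log option for this test. With about 205 patients this is adequate, and it tests H0 as written.
2. Keep the criterion of a mean above 50 nmol/L. Beside it, report at day 12–21 and week 13–16 the proportion of all verum patients with a sample who have 25(OH)D of at least 50 nmol/L, with a 95% CI.
3. Word the week 13–16 conclusion so that maintained sufficiency is not claimed from the mean alone.

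The cost is a change of wording and one extra estimate per time point from data already collected. The success statement may look less favourable.
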